## Abstract

**Background:**

Dengue is increasing in its global presence with an estimated 4 billion people at-risk of infection in at least 128 countries. Despite the promising results of EcoHealth and community mobilization approaches to *Aedes* reduction, more evidence of their efficacy on reducing dengue risk is needed. The principal research question is to determine if interventions based upon community mobilization reduce the risk of dengue virus infection among children 3 to 9 years old compared to usual dengue control practice in Fortaleza, Brazil.

**Methods:**

The present study will follow a pragmatic cluster randomized controlled trial (cRCT) design with randomization at the census tract level with equal allocation to the two arms. In each arm, there will be 34 clusters of 86 children between 3 to 9 years old for an expected total of 5848 children enrolled in the study, assuming a risk reduction of 29.5% based upon findings from a previous multi-site cRCT. The primary outcomes are rates of anti-dengue Immunoglobulin G (IgG) seroconversion and adult female *Aedes* density. The intervention is based upon a participatory health research approach, Socializing Evidence for Participatory Action (SEPA), where the research evidence is used to foster community engagement and ownership of the health issue and solution. Following allocation, intervention communities will develop and implement their own solutions that will likely include a wide variety of collective events and media approaches. Data collection activities over a period of 3 years include household visits for blood collection, household surveys, and entomological surveys; and qualitative activities including focus groups, in-depth interviews, and document analysis to evaluate the process, acceptability, fidelity, and sustainability of the intervention. Study participants will be aware of their assignment and all research staff will be blinded although the intervention assignment will likely be revealed to field staff through interaction with participants.

**Discussion:**

The results of our study will provide evidence on community mobilization as an intervention for dengue control. We anticipate that if community mobilization is effective in Fortaleza, the results of this study will help develop evidence-based vector control programs in Brazil, and also in other countries struggling with *Aedes*-transmitted diseases.

**Trial registration:**

ISRCTN66131315, registration date: 1 October 2018.

## Background

Dengue is increasing in its global presence with an estimated 4 billion people at-risk of infection in at least 128 countries [1–3]. Rising incidence and large-scale outbreaks are largely due to inadequate living conditions, naïve populations, rapid urbanization, global trade and population mobility, climate change, and the aggressive nature of the mosquito vectors *Aedes aegypti* and *Aedes albopictus* [4–6]. Poor quality housing and sanitation management, and high population density are key determinants of increased risk of infection at the population level [7, 8]. It is estimated that dengue, the fastest spreading mosquito-borne viral disease, infects 390 million people annually [4, 9] with a 30-fold increase in incidence during the past 50 years [10]. Dengue is highly endemic in Brazil with over 1.7 million cases reported for 2016 and 2017 [11, 12]. In Brazilian cities, the inconsistency in the supply of household piped water requires inhabitants to store clean water in water containers and water reservoirs creating ideal breeding sites for *Aede*s within and near the households [13].

There is no current treatment for dengue and vaccines are in different stages of commercial development, with one vaccine being licensed although its implementation is context specific [14–16]. Preventing or reducing dengue transmission primarily depends on controlling the mosquito vectors or interrupting human-vector contact. Many vector control options have been identified but the evidence of effectiveness is often conflicting or missing [17]. There is increasing resistance of the mosquitos to larvicides and insecticides, [18, 19] which have failed to contain *Aedes* expansion [20–22] or result in sustained reductions of mosquito populations [17]. In addition, there are important health concerns related to the chronic exposure of pesticides [23, 24]. A recent meta-review of systematic reviews stated that better quality studies of *Aedes* intervention studies are needed [17] with a systematic review of *Aedes* control randomized control trials demonstrated the promising results from community mobilization interventions [25].

With the cost and growing burden of dengue, it is an urgent priority to identify effective evidence-based control options [17, 21, 26] in endemic and at-risk regions. For dengue alone, worldwide estimates are as high as 39 billion USD per year on the costs of medical care, surveillance, vector control, and lost productivity [27]. Brazil is also prone to outbreaks of chikungunya and zika, which are transmitted by the same *Aedes* vectors. There were two waves of a chikungunya outbreak in 2016 and 2017 with a total of 445,274 cases [11, 12], and prior to the chikungunya outbreak, there was the introduction of zika. The zika outbreak began in 2015 and ended in 2017, which resulted in 231,566 cases, including 3014 cases of Congenital Zika Syndrome [28]. Given that immunity can be developed for chikungunya [29] and potentially for zika [30], and that the current number of cases for both diseases in Fortaleza is extremely low [31, 32], our study will focus on dengue infections.

A community mobilization trial, Camino Verde (IRSCTN27581154), based in Nicaragua and Mexico, demonstrated that community mobilization, as well as customization of activities to local contexts, were effective strategies for vector control and dengue reduction in a pesticide-free environment despite the differences between the two sites in socio-economic status, dengue prevalence, safety conditions, and community organization and support [7, 8]. Local pilot work conducted in Fortaleza included a cluster randomized controlled trial, which was conducted from 2012 to 2013 and demonstrated the effectiveness of an Ecohealth approach, including social participation, to reducing *Aedes* density [33]. Other local pilot work included a cluster randomized controlled which found that insecticide-treated curtains reduced seasonal dengue infections and *Aedes* mosquito density [34]. The design of our proposed trial is closely based on the Camino Verde study, which will occur in a different context in that it is highly urbanized and hyperendemic for dengue. We aim to evaluate the effectiveness of community mobilization in reducing the risk of dengue infections and mosquito infestation compared to usual dengue control practice in Fortaleza, Brazil.

## Objectives

The principal research question of this study is: does community mobilization reduce the risk of dengue virus (DENV) infection compared to usual dengue control practice in Fortaleza, Brazil? The specific objectives are 1) Measure the impact of the intervention on the risk of primary dengue infections using serological indicators in participating children; 2) Measure the impact of the intervention on human exposure to adult female *Aedes* in participating households; 3) Measure the impact of the intervention on self-reported dengue in participating households; 4) Explain the heterogeneity of the effect of community mobilization; 5) Analyze the acceptability of the intervention and the empowerment process of communities and individuals.

### Trial design

We will follow a parallel pragmatic cluster randomized controlled trial (cRCT) design with randomization at the census tract level with equal allocation to the two arms, to evaluate the effectiveness of community mobilization measured by the risk of primary DENV infection, self-reported dengue cases, and *Aedes* infestation rates. The quantitative baseline assessment will include a household questionnaire, entomological evaluation of households and high-risk communal areas, and blood samples (from finger pricks) from children aged 3–9 years. Following the baseline assessment, allocation will occur after which community mobilization activities will begin for a period of 24 months. Baseline community interviews and focus groups for the qualitative studies will be performed just after allocation.

This is an investigator-initiated trial that was registered with ISRCTN66131315 prior to enrollment. The trial protocol was developed according to the Standardized Protocol Items: Recommendations for Interventional Trials (SPIRIT) guidelines (Additional file 1) [35].

### Methods: participants, interventions, and outcomes

#### Study setting

The city of Fortaleza, capital of Ceará State, is situated on the Atlantic coast of north-eastern Brazil with a rainy season from January to May. Fortaleza is vulnerable to infestation of *Aedes aegypti* due to its tropical climate, high population density and rapid population growth (4.9%; from 2010 to 2014 [36]), and inadequate sanitary conditions [33, 37]. Irregular water supply leads people to store water in various containers such as water tanks, cisterns, barrels, drums, bowls, and pots. Fortaleza is particularly burdened by arboviruses. From 2016 to 2017, there were 35,159 cases of dengue, 79,486 cases of chikungunya, 1598 cases of zika, and 52 cases of congenital zika syndrome reported in Fortaleza [31, 32, 38]. It is important to note zika cases began to appear in large numbers in Fortaleza in 2015 although the compulsory notification did not begin until 2016. There are two currently circulating dengue serotypes in Fortaleza, DENV1 and DENV2 [39], with the public health officials anticipating the possibility of reintroduction of DENV3 within the next few years.

Standard dengue control practice activities of the Fortaleza Municipal Health Secretariat include periodic visits of houses and high-risk *Aedes* breeding grounds in communal areas (e.g., scrapyards, tire repair shops, etc.) by vector control agents for habitat destruction and application of the larvicide, Diflubenzuron, for containers that cannot be cleaned [40]. In Brazil, the use of temephos as a larvicide was discontinued in 2010 due to increased resistance and toxicity and the general population of Fortaleza do not have access to larvicides for domestic purposes. The Vector Control Department within the Fortaleza Municipal Health Secretariat is responsible for community education and mobilization actions in areas of higher transmission risk.

#### Eligibility criteria

During enrollment visits, all households in selected clusters with children from 3 to 9 years will be eligible and asked to participate in the trial [41]. Eligibility will be evaluated on three levels: cluster, household, and individual. The inclusion criteria will be: 1) any of the 3020 census tracts from the 2010 Census; 2) households permanently inhabited; 3) children aged 3 to 9 years. The exclusion criteria will be: 1) census tracts where interventions outside of vector control standard practices occurred within the last 5 years; 2) census tracts deemed to be too insecure for study personnel (determined based upon the opinion of the research team and stakeholders); 3) clusters with less than 230 households as previous work has shown that 230–240 households are required to obtain the needed sample size [8]; 4) abandoned or non-permanent households; 5) households with the intention to move outside of the household during the study period; 6) children with chronic disease or other health condition that preclude participation in the study; and 7) parents or guardians who are unable to give informed consent.

#### Intervention

Socializing evidence for participatory action (SEPA) is an approach to health promotion and community development based on the production and use of research evidence [7, 42]. Critical to SEPA is the socialization of research evidence to communities and leadership to foster engagement in finding solutions and local strategies to their own health problems. At allocation, community engagement will begin by presenting each intervention cluster with their baseline results through community meetings and household visits using community volunteers and facilitators from the research team. Volunteers from the communities will serve as organizers and educators trained by facilitators from the research team. Intervention design groups will be organized in each cluster with community members, including a subsample of people with opinions on vector control interventions, for the development and design of the customized vector control activities and the implementation process. Customized community activities will be developed during community meetings and based on pilot studies may include: i) neighbourhood clean-up campaigns; ii) distribution of intervention package to promote research activities and efforts to reduce vector breeding sites; iii) collaboration with community and municipal services to improve garbage collection and to cover collection bins (highly productive breeding sites of *Aedes* [43, 44]); iv) school visits; v) artistic demonstrations or sport competitions; vi) SMS communication. Community activities will be continually adapted post-implementation while ensuring a rigorous documentation of the process and evolution with the facilitators monitoring and documenting community activities. Intercommunity (or intercluster) visits will be organized for volunteers of each cluster to share experiences between communities and to strengthen the group dynamics and the collective preventive action. Community-to-community monitoring will allow volunteers to gather both quantitative and qualitative information and will be opportunity to provide peer-encouragement and training for intervention field staff and communities.

We expect a high level of compliance, above 95%, in the activities chosen by the community against *Aedes* based on experience from preliminary work [33, 45]. The content, coverage, frequency, and duration of community and household participation and activity in community mobilization will be monitored through the fidelity and process analyses [46, 47]. Our long-term relationships with local stakeholders and field staff will facilitate the engagement of households and communities and we will ensure engagement through i) using baseline survey results [7], ii) implementation of a local steering committee involving community representatives, and iii) involving community members in the evaluation process through a participatory evaluation and interpreting the heterogeneity assessment of impact.

The control and intervention arms will receive standard practices of vector control of the Fortaleza Municipal Health Secretariat during the trial including periodic visits of houses and high-risk *Aedes* breeding grounds in communal areas (e.g., scrapyards, tire repair shops, etc.) for habitat destruction and application of larvicide and insecticide when necessary, and health education activities, provide by vector control agents.

#### Outcomes

Primary outcomes are: rates of anti-dengue Immunoglobulin G (IgG) seroconversion (from negative to positive at follow-up) to evaluate the incidence of primary infections, and adult female *Aedes* density (number of adult female *Aedes* per household). Additional measurement of the antibodies waning rate or disappearance of detectable IgG antibodies (from positive at baseline to negative at follow-up), which may happen one to 2 years after primary dengue infections will determine the impact of the intervention on subsequent dengue secondary infections [48]. Secondary outcomes captured during household visits at baseline and follow-up are: i) anti-dengue IgG antibodies waning rates; ii) self-reported dengue during the most recent dengue season; iii) entomological indices: the container index (number of positive containers per household) and the premise condition index (how well the structure is maintain and yard), and, iv) knowledge, attitudes, and practices (KAP) for dengue control that will combined to create an index [49]. Secondary outcomes captured from the household survey, community focus groups, and in-depth individual interviews include: i) social acceptability of activities; ii) implementation fidelity and adaptability processes; iii) potential for sustainability, and iv) empowerment of individual and communities.

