#### Participant timeline

Household visits for the questionnaire will occur at dry season and rainy season baseline and at endline (Figs. 1 and 2). The seroprevalence baseline and follow-up surveys will occur yearly (for 3 years), 5 months after the rainy season peak to allow the maximum levels of IgG to be reached without residues of other immune reactions to cross-react [50]. A baseline entomological survey will occur in rainy season, the same period as the household questionnaire. Following baseline, entomological surveys will occur yearly during the rainy season. Community focus groups and interviews will occur twice a year, starting with the baseline assessment.

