#### Recruitment

Based on preliminary and exploratory studies [7, 8, 45, 53, 54], we observed high participation rates in seroprevalence surveys (93% to 100%) and the finger prick in children to collect blood samples was well accepted [45, 53–56]. During door-to-door enrolment visits the research teams will be assisted by community workers and volunteer facilitators to explain the aim and importance of the research to families. The starting point of household recruitment will be the centroid (as determined by QGIS) of each selected cluster with a radial pattern of household recruitment from the starting point, following the pattern of city blocks within the cluster.

Eligibility criteria of the household and individual will be verified. The goals of the study and all procedures will be detailed following a pre-established script, the consent forms will be explained, and we will allocate adequate time to answer any prospective participant questions. Immediately after enrolment and consent of participation, entomological data collection and/or blood collection, as well as questionnaires administration will occur.

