#### Allocation

After both baseline collections, the rate of IgG seroconversion of each cluster will be calculated. Based on the overall distribution of seroconversion rate, there will be five risk strata created and each cluster from the baseline assessment will then be assigned to a risk stratum. A computer generated (block) randomization of each enumerated member of the strata will be assigned to either the intervention or control arm.

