## Trial status

Recruitment of participants began on 15 November 2019 and will be completed by 30 June 2020. The protocol version number is COESA-FORTALEZA-2019, dated 15 December 2019.

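### On the scheduled order of events, dengue infections from before allocation can count as primary seroconversions in both arms and pull the risk ratio towards 1; the baseline serology passages also conflict.

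*Protocol article*

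**What the plan says.** The Outcomes section defines the first primary outcome as "rates of anti-dengue Immunoglobulin G (IgG) seroconversion (from negative to positive at follow-up) to evaluate the incidence of primary infections". It does not name the sample that must be negative, and it does not tie the interval to allocation.

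The order of events comes from several sections of the protocol article:

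- **Study setting:** Fortaleza is described "with a rainy season from January to May".
- **Participant timeline:** "The seroprevalence baseline and follow-up surveys will occur yearly (for 3 years), 5 months after the rainy season peak". For the questionnaire, "Household visits for the questionnaire will occur at dry season and rainy season baseline and at endline". The entomological baseline is in the rainy season. No blood survey is named there.
- **Trial status:** "Recruitment of participants began on 15 November 2019 and will be completed by 30 June 2020".
- **Recruitment:** "Immediately after enrolment and consent of participation, entomological data collection and/or blood collection, as well as questionnaires administration will occur".
- **Allocation:** "After both baseline collections, the rate of IgG seroconversion of each cluster will be calculated". Those cluster rates then form the five randomization strata.
- **Trial design:** "Following the baseline assessment, allocation will occur after which community mobilization activities will begin for a period of 24 months".

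Statistical methods gives a log-binomial mixed model with one fixed intervention effect. Its random effects are for stratum, measurement period (baseline and two follow-ups), household and census tract.

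**The concern.** An infection that occurs before the intervention starts cannot be prevented by it. If the negative reference sample precedes a transmission season that is over, or partly over, before allocation, infections from that season appear as conversions at the next yearly sample. They are expected at the same rate in both arms. They add equal risk to each arm and move the risk ratio towards 1, so an effective intervention could look weak or null. The sample size makes no allowance for this.

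There is also a contradiction. A seroconversion rate needs two samples per child, yet the Allocation section calculates one per cluster before randomization, while Participant timeline schedules a single baseline blood survey. The answer matters twice: it decides how the strata are formed, and whether a later pre-allocation sample exists from which the outcome could start.

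**Working it through.** **Step 1. Order of events.** Recruitment opens on 15 November 2019, before the January to May 2020 rains. Allocation follows both baseline collections, which Participant timeline describes as dry season and rainy season, so it cannot precede the rainy-season baseline. Mobilization follows allocation. Blood is yearly, so a child bled in November or December 2019 is next bled after the 2020 rains. For that child the whole 2020 season lies between reference sample and intervention. For a child bled between January and May 2020, part of it does.

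**Step 2. Does the model remove these events?** No. A period term absorbs differences in overall risk between intervals. The single intervention effect is still an average over an interval in which the arms should not differ because of the intervention and one in which they may. Nothing sets the intervention term to zero before allocation.

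**Step 3. Reproduce the planned size.** Inputs from Sample size: risks 0.30 and 0.2115 (risk ratio 0.705), ICC 0.07, 60 analysed children per cluster, 32 clusters per arm. I take the 0.05 level as two-sided.

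- Design effect: 1 + 59 × 0.07 = 5.13. Effective n per arm: 32 × 60 / 5.13 = 374.3.
- Power = Φ(|p1 − p2| / √[(p1q1 + p2q2)/n] − 1.96), where q = 1 − p.
- Standard error: √[(0.2100 + 0.1668)/374.3] = 0.0317. Then 0.0885/0.0317 − 1.96 = 0.83, which gives 79.7%.

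The planned 80% is reproduced.

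**Step 4. Reading A: 0.30 is the total risk from baseline, and a share f of control-arm events arises before allocation.** The documents do not give f; 10% to 50% is an assumed range, and 50% corresponds to one of two equal yearly intervals.

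- All events counted: control risk 0.30, risk ratio f + (1 − f) × 0.705.
- Only post-allocation events counted: at-risk children per cluster m = 60 × (1 − 0.30f), control risk 0.30(1 − f)/(1 − 0.30f), risk ratio 0.705, design effect 1 + (m − 1) × 0.07.

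| f | Risk ratio, all counted | Power, all counted | m | Control risk, post only | Power, post only |
|---|---|---|---|---|---|
| 10% | 0.734 | 70% | 58.2 | 0.278 | 75% |
| 33% | 0.803 | 44% | 54 | 0.222 | 62% |
| 50% | 0.853 | 27% | 51 | 0.176 | 50% |

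(The 33% row uses f = 1/3.)

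At f = 50%, all counted: the intervention risk is 0.30 × 0.8525 = 0.2558 and the difference 0.0442; √[(0.2100 + 0.1903)/374.3] = 0.0327; 1.353 − 1.96 = −0.607, giving 27%. Post only: risks 0.1765 and 0.1244, design effect 4.5, n = 32 × 51 / 4.5 = 362.7, giving 50%.

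**Step 5. Reading B: 0.30 is the post-allocation risk and an earlier season adds risk q.** All counted: control q + (1 − q) × 0.30, intervention q + (1 − q) × 0.2115. Post only: 0.30 against 0.2115 with m = 60(1 − q).

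| q (assumed) | Risk ratio, all counted | Power, all counted | Power, post only |
|---|---|---|---|
| 0.05 | 0.749 | 72% | 79% |
| 0.10 | 0.785 | 64% | 79% |
| 0.20 | 0.839 | 51% | 78% |

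Both readings keep the ICC at 0.07 and the risk ratio at 0.705 in the exposed interval.

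**The case against.** The strongest reply is that the timing is pieced together. No allocation date is given and the timeline figures are not shown. Recruitment allows entomology and/or blood at enrolment, so the November start does not prove that blood was drawn then. A survey five months after a peak within January to May falls between June and October, which does not fit a November start. If all baseline blood were taken after the 2020 rains and just before allocation, the problem would disappear. This stands as a limit on certainty. It is the less natural reading, because recruitment closes on 30 June 2020 and blood collection is linked to enrolment.

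Second, a pre-allocation seroconversion rate and a separate baseline period in the model may mean that a second early sample exists and that its conversions are handled apart. That is possible, but no section makes such a sample the reference. Data quality assurance retests baseline and follow-up pairs, which points to baseline as the reference without saying which baseline sample.

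Third, naming the reference sample could be left to an analysis plan. However, this article itself fixes the outcome, the order of events and the model, and its baseline serology passages conflict.

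A reader might infer that a full season precedes allocation for every child. The documents do not support that, since enrolment runs to 30 June 2020. A reader might also attribute the whole fall from 80% to 27% to counting early events. At a one-half share, power is only 50% even when they are excluded, so 30 of the 53 percentage points come from the lower exposed risk that the scenario assumes.

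**Conclusion.** The concern holds conditionally. Followed as written, the schedule lets pre-allocation infections count as primary events for children bled before or during the 2020 season. The direction of the resulting bias, towards a risk ratio of 1, does not depend on how many such infections there are.

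The size cannot be fixed from the article, because neither the allocation date nor the time span of the 0.30 risk is stated. The power lost by counting these events is about 5, 18 and 23 percentage points at shares of 10%, one third and 50% under reading A, and about 7 to 27 points under reading B. To say that most of the planned power is lost would go beyond the documents.

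The conflict between one scheduled baseline blood survey and a pre-allocation seroconversion rate needs no assumption and has to be resolved in any case.

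**What to change.** 1. State the dates of baseline blood collection and of allocation, and reconcile Participant timeline with Allocation: either the strata use baseline seroprevalence, or a second pre-allocation sample exists and should appear in the schedule.
2. Define the primary seroconversion interval as starting at the last sample before allocation, with children positive at that sample outside the risk set.
3. If the only pre-allocation sample precedes the 2020 season, do not let the first interval drive the intervention contrast. One way is to estimate the effect by interval, take the interval or intervals wholly after allocation as the main estimate, and report the all-interval intention-to-treat estimate as a sensitivity analysis.
4. Restate the control risk, its time span and the power for the exposed interval.

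This changes wording and analysis only and needs no new samples. It leaves fewer children at risk and a shorter counted interval. In the single-sample case the risk set is also defined shortly after allocation, by a measurement taken once mobilization may have begun, and infections between allocation and that sample are not counted. That is a real departure from a risk set fixed at randomization. It is why step 3 applies only if no later pre-allocation sample exists, and why the all-interval estimate should be reported beside it.
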